## **TREATMENT**

Eligible patients for whom informed consent has been obtained will be randomized to either of the three treatment regimens using a computer generated randomization code provided.

### **Drug Administration:**

SSG will be given IM or IV at a dosage of 20mg/kg/day\* for 30 days.

PM will be given IM at a dosage of 15 mg/kg/day for 21 days.

SSG + PM combination: SSG will be given IM or IV at a dosage of 20mg/kg/day\* for 17 days and PM at a dosage of 15 mg/kg/day IV/IM for 17days

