## **Clinical Pharmacology**

### ***Pharmacokinetics***

An HPLC assay was developed at the University of Illinois at Chicago under GLP conditions in order to be able to determine the concentration of paromomycin in biological fluids (e.g. urine and plasma)

Single Dose Intramuscular Pharmacokinetics in Healthy Normal Volunteers

Sixteen HNVs were given a single IM dose of paromomycin base either 12 or 15 mg /kg (8 per group)

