## **HYPOTHESIS**

That a combination course of SSG and PM (17 days) is similar in efficacy to either PM alone(21 days) or SSG alone (30 days) and that the shorter course combination (17 days) is not more toxic than PM or SSG alone.

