## **METHODOLOGY**

### **STUDY DESIGN**

This will be a multi-centre, prospective, open, parallel group, comparative trial of efficacy and safety of SSG alone given IM/IV (according to usual hospital practice) for 30 days versus paromomycin alone given IM for 21 days versus a combination of SSG and PM given for 17 days, in the treatment of patients suffering from VL in Ethiopia, Kenya and Sudan.

Patients who have clinical symptoms and a confirmed parasitological diagnosis of VL by splenic aspirate, lymph nodes aspirate or bone marrow aspirate (to be specified for each hospital site) and who have fulfilled the inclusion/exclusion criteria will be enrolled.

The primary endpoint will be cure rate at 6 months post treatment. Secondary endpoints will be cure rate at end of treatment (Day 31 for SSG, Day 22 for PM, Day 18 for PM + SSG) and at three months post treatment.

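### The dosing instruction allows intravenous paromomycin in the combination arm only: a minor inconsistency, probably a drafting slip

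*Protocol*

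**What the plan says.** The Drug Administration section is the instruction from which staff dose. For PM alone it states: "PM will be given IM at a dosage of 15 mg/kg/day for 21 days". For the combination it begins "SSG + PM combination: SSG will be given IM or IV at a dosage of 20mg/kg/day" and, in the same sentence, continues "PM at a dosage of 15 mg/kg/day IV/IM for 17days".

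The Study Design section gives "SSG alone given IM/IV (according to usual hospital practice) for 30 days" for the SSG arm and "paromomycin alone given IM for 21 days" for the PM arm. The third arm is described only as "versus a combination of SSG and PM given for 17 days", with no route for either drug.

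The Hypothesis section sets a safety comparison between the arms: "the shorter course combination (17 days) is not more toxic than PM or SSG alone". The Pharmacokinetics section reports the only human kinetic data for PM: "Sixteen HNVs were given a single IM dose of paromomycin base either 12 or 15 mg /kg".

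**The concern.** The same drug at the same daily dose has one permitted route in one arm and two in the other, and nothing in the available text says why or when the second may be used. Two things are at stake.

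- **Conduct.** A nurse or clinician following the dosing section could properly give PM intravenously to a combination patient. The protocol shows no human kinetic data for that route and gives no administration instructions for it.
- **Interpretation.** The hypothesis includes toxicity relative to PM alone. If some combination patients received PM intravenously and no PM-alone patient did, route would be tied to arm in an open-label trial. Local tolerability is the clearest outcome that route could affect. Injection-site pain is the most frequent reaction in the Japanese safety data that the protocol cites (94 of 2,220, or 4.2%), although that section does not state the route used.

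**Working it through.** The plan attaches no figure to this point, so the check is a comparison of text, with short arithmetic to place it in scale.

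**Step 1. Routes, section by section.**

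| Drug and arm | Study Design | Drug Administration |
|---|---|---|
| SSG alone, 30 days | IM or IV, by hospital practice | IM or IV |
| PM alone, 21 days | IM | IM |
| SSG in combination, 17 days | not stated | IM or IV |
| PM in combination, 17 days | not stated | IV or IM |

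**Step 2. Each drug across the arms that contain it.** SSG has the same two routes in both of its arms. PM has one route in one arm and two in the other. The asymmetry therefore concerns PM only.

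**Step 3. Search for a reconciling rule.** The only rule for choosing a route is the hospital-practice clause, and it is attached to SSG alone. The Serious Adverse Events section says only that treatment is parenteral, which fits either route. No section gives a dilution, an infusion time or a criterion for intravenous PM. The contents list places a study sites section between study design and inclusion criteria. That section is not in the available text, so the statement that no rule exists is limited to what is.

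**Step 4. Support for the route.** The human kinetic data are single-dose and intramuscular, in 16 volunteers (8 at each of two doses). The clinical experience with PM is summarised without a route, so it neither supports nor rules out intravenous use.

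**Step 5. Differences already present between the two PM arms.**

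- Total PM, combination: 15 mg/kg/day × 17 days = 255 mg/kg.
- Total PM, PM alone: 15 mg/kg/day × 21 days = 315 mg/kg.
- Difference: 315 − 255 = 60 mg/kg, and 60/315 = 19% less in the combination.
- The combination also adds 17 days of SSG.

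Route would be a further difference on top of these two, and the only one that is not part of the regimens being compared.

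**Step 6. What is not touched.** The sample size uses cure rates only: 10.5 × (0.85 × 0.15 + 0.95 × 0.05)/0.01 = 10.5 × 0.175/0.01 = 183.75, which rounds up to the protocol's 184 per arm. Route does not enter it. The efficacy comparison is of whole regimens as assigned, and the 5% significance level and 90% power are unchanged.

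**The case against.** The strongest reply is that this is a slip with no shown consequence. The SSG half of the same sentence allows both routes, every other statement of PM route in this trial says IM, and no practical instructions for intravenous PM appear. The hypothesis compares regimens that already differ in drugs, duration and PM dose. The protocol's one statement about what drives PM oto- and renal toxicity, in the Japanese safety data, names total dose and duration and not route. The Study Design summary omits the SSG route for the combination as well, so its silence is not special to PM. All of this stands, and it keeps the point minor. It does not defend the wording, because a slip in the operative dosing text can still be followed.

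A reader might infer more than the documents support:

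- **That intravenous PM was intended or given.** Nothing shows this.
- **That the toxicity comparison is biased.** That depends on intravenous use, which is unknown, and on a route effect that the documents do not quantify.
- **That the animal tables show a clinical hazard.** The acute data include intravenous dosing, but only in mice. They give no intravenous and intramuscular pair in the same species, and single-dose lethality in mice does not measure the risk of repeated doses in patients.
- **That route would go unrecorded.** The treatment sheet is described by time of dosing and signature, but neither the sheet nor the case report form is shown, so the absence of a route field cannot be established.

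**Conclusion.** The inconsistency is real and is confirmed by the text: PM is intramuscular only when given alone, and intravenous or intramuscular in the combination, with no reason or rule in the available protocol. Severity is minor. Confidence is high about the wording and low about any practical impact. The consequence is conditional: only if a site uses the intravenous option does route become an avoidable, arm-specific difference in the toxicity comparison with PM alone. Its size cannot be stated. A count of doses that the text would permit intravenously would measure the size of the arm, not the size of an effect.

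The conclusion assumes that the Drug Administration section is what sites follow and that no document outside the available text fixes the route.

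**What to change.** In Drug Administration, change IV/IM to IM for PM in the combination arm. Naming the PM route for the combination in Study Design as well would be helpful tidying.

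If intravenous PM is truly intended, state the reason and apply the same route rule to both PM arms. In that case it would also be sensible to confirm that the treatment sheet or case report form captures the route given.

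The main correction removes one route from one line. It needs no change to endpoints, sample size or analysis.

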**\*The maximum dosage of SSG per day for any patient is 850mg (8.5ml)**

Treatment will be given by the clinicians/nurse at the same time each day and a treatment sheet indicating time of dosing bearing the signature of the attending clinician/nurse will be kept.

### **Rescue medication**

In the event of failure to respond to treatment, clinical deterioration or relapse at any time during the study, rescue treatment consisting of IV Ambisome® ( a liposomal formulation of amphotericin B) at a dosage of 3 mg/kg/day for 5 days or according to local Ambisome® rescue protocol, the exact regimen used at each trial site to be documented in the case report form..

### **Prior and Concomitant Medications**

No additional anti-leishmanial therapy will be permitted during the course of the study. If such therapy becomes necessary, the patient will be withdrawn from the study and considered a treatment failure.

Concomitant medication necessary for the health of the patient will be permitted during the course of the study. This will include the concomitant use of drugs such as paracetamol as an analgesic/antipyretic. Details of all concomitant medication taken during the study will be recorded in the CRF with indication, daily dose, route and dates of administration.

In the case of a patient presenting with co-infection, eg. pneumonia or malaria, these infections should be treated first. The patient should be re-assessed for suitability for inclusion in the trial after one week.

### **EFFICACY ASSESSMENT**

Efficacy will be assessed using clinical, haematological, biochemical and parasitological responses.

- **Clinical Assessment**

The clinical evaluation will involve measuring the spleen size by palpation below the left coastal margin, temperature, blood pressure, body weight on days 0, 7, 14, 21 and end of treatment (18, 22, 31), 3 months and 6 months post treatment.

ECG and audiometry will be done at baseline, day 14, end of treatment and 6 months follow-up, in selected sites.

## **FINAL VERSION LEAP 0104 31 JULY 2004 CONFIDENTIAL**

- Haematological and biochemical assessment

Blood will be analyzed for haemoglobin, WBC, platelets, urea, creatinine, and liver function tests on days 0, 7, 14, 21 and end of treatment (18, 22, 31), 3 months 6 months post-treatment.

- Unanalysis

Urinalysis will be performed on days 0, 7, 14, 21 and end of treatment (18,22,31) 3 months and 6 months post-treatment.

- Parasitological assessment

Parasitological assessment involves aspirating the spleen, lymph node or bone marrow at baseline, end of treatment (18, 22, 31 days depending on treatment arm) on, and at 3 months and 6 months follow up visits for all study patients. In addition, at selected sites aspirates will be cultured. Each patient will have a maximum of four aspirates. Patients who are clinically well with no signs or symptoms of VL and no palpable lymph nodes / spleen at the three months visit do not to have any aspirate at this visit. All patients will have an aspirate at 6 months post treatment.

The source of parasitological specimens should remain unchanged throughout the treatment and follow up periods, unless the spleen / lymph node initially chosen as the source of parasitological specimens becomes unpalpable, in which bone marrow aspirate should be performed.

Since bone marrow, lymph node and splenic aspirates are invasive procedures, these should only be performed at other times if clinically indicated.

### **PRIMARY EFFICACY ENDPOINT**

The primary efficacy variable is parasitological clearance at 6 months post treatment by splenic, lymph node, or bone marrow smear.

### **SECONDARY EFFICACY ENDPOINT**

The secondary efficacy endpoint will be parasitological clearance at the end of treatment (18, 22, 31 days depending on treatment arm – Test of cure (TOC)) and at 3 months post treatment.

## **SAFETY ASSESSMENTS**

During treatment and at follow up, safety will be assessed by means of haematological, urinalysis and biochemical monitoring as above, and by ECG and audiometry at selected sites. In addition, patients will be asked at each visit if they have suffered any side-effects or other unexpected adverse events.

### **Adverse events**

An adverse event will be defined as any noxious, pathological or unintended change in anatomical, physiological or metabolic functions as indicated by physical signs, symptoms and/or laboratory changes occurring in any phase of the clinical study, whether or not they are considered to be associated with the study drug. This includes an exacerbation of pre-existing conditions or events, intercurrent illnesses, drug interaction, or the significant worsening of the disease under investigation that is not recorded elsewhere in the CRF under specific efficacy assessments. Anticipated day to day fluctuations of pre-existing conditions, including the disease under study, that does not represent a clinically significant exacerbation or worsening of the condition, will not be considered adverse events.

All adverse events occurring after the start of the study (defined as when informed consent was obtained) are to be reported. This is regardless of whether or not they are considered to be drug related. Adverse event (AEs) elicited by the investigator asking the patient or the patient's parent or guardian a non-leading question such as "Do you/has your child felt different in any way since starting the new treatment/the last assessment?" If the response was "Yes", the nature of the event, the date and time (where appropriate) of onset, the duration, maximum intensity (see below) and relationship to treatment are to be established (see below). Details of any changes to the dosage schedule or any corrective treatment are to be recorded on the appropriate pages of the CRF.

### **Assessment of Intensity/Severity**

The assessment of intensity/severity will be based on the investigator's clinical judgment. Maximum intensity/severity will be assigned to one of the following categories.

## **FINAL VERSION LEAP 0104 31 JULY 2004 CONFIDENTIAL**

**Mild:** An adverse event, which is easily tolerated by the patient, causing minimal discomfort and not interfering with every day activities.

**Moderate:** An adverse event, which is sufficiently discomforting to interfere with normal everyday activities.

**Severe:** An adverse event, which prevents normal everyday activities.

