## **FINAL VERSION LEAP 0104 31 JULY 2004 CONFIDENTIAL**

normal clinical practice when treating patients with VL. However, the frequency of testing might be increased depending on the patient's response to treatment.

Children will be included in this study because they represent more than 50% of VL cases in this region.

The effective treatment of VL benefits not only the individual patient but also the community by reducing the reservoir of infection for onward transmission by the sandfly vector. The evaluation of new and better treatments for VL, including shorter courses and combinations is anticipated to have a positive effect on development of parasite resistance and will reduce hospitalisation costs. If paromomycin is found to be efficacious and safe, it will be registered for the treatment of VL, providing a new alternative to treatments already available.

Patients will experience some pain while blood is drawn during venepuncture. The amount of blood to be drawn will be 10 mls before treatment and 7 mls at each subsequent visit, with a total of 42 mls (PM alone and a combination of PM and SSG), 49 mls (SSG alone) over the 6 months study period.

SSG has been extensively used in Sudan, Ethiopia and Kenya. Known adverse events include cardiac, muscle, joint and renal toxicity. PM has been used in clinical trials in Sudan and Kenya during the 1990's, and more recently in humanitarian emergency setting in Sudan. Known adverse events of the aminoglycosides include ototoxicity and renal toxicity.

Patients who are found to be HIV positive will be offered anti retroviral treatment at no cost in accordance with national guidelines for treatment.

A Data Safety and Monitoring Board (DSMB) will be set up to regularly review safety data.

Patients will be reimbursed for travel to and from the study site and will not receive any payment for trial participation. Any medication that is required during the trial period will be provided free of charge to the patient.

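### The only severity scale grades adverse events by discomfort and lost activity, so a symptomless creatinine, ECG or audiometry change fits only the mild grade whatever its size

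*Protocol*

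**What the plan says.** The Adverse events section defines an adverse event as an unwanted change in bodily structure or function, "as indicated by physical signs, symptoms and/or laboratory changes occurring in any phase of the clinical study". Laboratory changes are therefore adverse events in their own right, with or without symptoms.

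The section Assessment of Intensity/Severity gives the only grading rule. Its basis is stated first: "The assessment of intensity/severity will be based on the investigator's clinical judgment". The choice is then closed: "Maximum intensity/severity will be assigned to one of the following categories". The three categories are:

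- The lowest grade, mild, is for events that the patient bears easily, with little discomfort and no effect on daily life.
- The middle grade, moderate, is defined as "An adverse event, which is sufficiently discomforting to interfere with normal everyday activities".
- The highest grade, severe, is for events that stop the patient's ordinary activities altogether.

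Under Safety Assessments, "safety will be assessed by means of haematological, urinalysis and biochemical monitoring as above, and by ECG and audiometry at selected sites". On the risks, Ethical Considerations lists cardiac, muscle, joint and renal toxicity for SSG, and for the class to which PM belongs it says: "Known adverse events of the aminoglycosides include ototoxicity and renal toxicity".

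The Hypothesis section includes a safety claim: the 17-day combination should be no more toxic than either drug alone.

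**The concern.** The scale measures how an event feels and what it stops the patient doing. Several of the toxicities that the protocol expects are found by measurement, often before the patient notices anything, which is a good reason to schedule creatinine for everyone and ECG and audiometry where available. A scale built on discomfort cannot separate a trivial silent change from a large one.

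The trial's safety hypothesis is comparative. If severity grades are used to compare the arms, they will respond to symptomatic events such as injection pain and hardly at all to silent renal, cardiac or hearing changes. If investigators use their own judgment to grade such changes higher, they will do so without a common rule and knowing which treatment the patient received.

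**Working it through.** No arithmetic applies, and the protocol gives no figure to reproduce. The check is to read the grading rule against the rest of the protocol.

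**1. Are silent findings within the rule?** Laboratory changes are named in the definition of an adverse event. ECG and audiometry changes are not named, but the definition covers changes in physiological function, and I take a measured fall in hearing or an abnormal tracing to be one. The rule for assigning severity makes no exception for events without symptoms.

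**2. Which grade can a silent finding meet?** Take a patient with a clear rise in creatinine who feels no different.

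| Grade | What its definition requires | Met by a symptomless change? |
|---|---|---|
| Mild | Easily tolerated, minimal discomfort, activities unaffected | Yes |
| Moderate | Enough discomfort to interfere with activities | No |
| Severe | Activities prevented | No |

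The size of the change enters none of the three definitions, so the result is the same for a small rise and a large one. The same reasoning applies to a silent ECG abnormality or a loss of high tones seen only on audiometry.

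**3. Does another section grade by size?** No. The Exclusion Criteria set limits for haemoglobin, white cells, platelets, liver tests and creatinine, and exclude abnormal ECGs and clinical hearing loss, but these decide entry only. The sections Assessment of Causality and Serious Adverse Events give no severity grades.

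**4. Are the affected measures the ones that matter here?** Largely yes. The section on historical Japanese safety data describes ear and kidney toxicity as the main dose-limiting toxicities of injectable PM. In the 13-week dog study (Table 3), the low dose produced slight to minimal renal damage and hearing loss at high tones. For SSG, the SSG section and Ethical Considerations both name cardiac and renal toxicity. Muscle and joint toxicity, also named for SSG, are more likely to be felt, and the functional scale suits them better.

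**5. What does the scale register well?** Symptoms. In the Japanese data the commonest reaction was injection-site pain, in 94 of 2,220 patients (94 / 2,220 = 4.2%). Such pain can be graded moderate or severe under the wording; a silent creatinine rise of any size cannot.

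**6. How widely does this apply?** Blood chemistry is scheduled for all patients, so the renal part of the problem covers the whole trial. ECG and audiometry are done at selected sites, so the cardiac and ear parts arise only there. The sample size table lists five teams, and the Study Design section says that the trial is open; judgment without a numeric rule can therefore vary between sites and with knowledge of the treatment.

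**The case against.** The strongest reply has four parts.

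- **Judgment governs the grade.** The protocol rests severity on clinical judgment, so an investigator need not call a large creatinine rise mild. This stands in part: the wording does not guarantee a mild grade in practice. But judgment has to end in one of three functional definitions, and a higher grade for a silent change departs from them. The outcome is inconsistency, not a repair.
- **The scale is meant for symptoms.** The Adverse events section ties the recording of maximum intensity to a positive answer when the patient is asked about feeling different, and Safety Assessments treats measurements as a separate stream. This is a fair reading of the workflow. It leaves the definition, which includes laboratory changes, without a suitable grade.
- **Nothing is lost.** This stands, and it limits the point. A reader might infer that organ toxicity would be hidden. The documents do not support that: values are collected at scheduled visits, and the Serious Adverse Events section makes reportable any experience that the investigator regards as serious or as suggesting a significant hazard, whatever its severity grade. Seriousness is, however, a separate classification and supplies no grade.
- **The consequences are not written down.** A reader might infer that the data safety and monitoring board would work from these grades, or that the safety hypothesis would be decided on tables of severity by arm. The protocol says only that the board reviews safety data, and its Analysis section describes no such tables. Both are inferences.

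A reader might also add liver damage to the named toxicities. Liver tests are monitored, but liver toxicity is named for neither drug.

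**Conclusion.** The point holds as a weakness in a stated rule. The protocol's one severity scale is functional, it takes in adverse events that are defined to include laboratory changes, and by its wording a symptomless change in creatinine, ECG or audiometry fits only the mild grade. Grades for renal, cardiac and ear toxicity are therefore likely to be uninformative if the wording is followed, and inconsistent between sites and arms if it is not. Either way, severity comparisons bearing on the hypothesis of no greater toxicity are weakened.

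The size cannot be put as a number, because the protocol gives no expected rate of silent changes under these regimens. The conclusion rests on two assumptions: that ECG and audiometry changes count as adverse events under the general definition, and that severity grades will be used when the arms are compared. The measured values remain available, so this is a correctable defect in grading and not a loss of safety data. It should be changed, but it does not threaten the trial.

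**What to change.** Keep the present three grades for events that the patient feels. For laboratory, ECG and audiometry findings, assign severity from the measured value on a published numeric toxicity scale, with age-appropriate ranges because patients from 4 to 60 years are eligible, and fix the scale before enrolment. Where an event has both a measured change and symptoms, record the higher grade. State that ECG and audiometry grades exist only for the sites that perform those tests.

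The cost is a change of wording in the protocol and the case report form. No new test is needed: the grades come from measurements already scheduled and can be derived in the database, provided that the case report form captures ECG and audiometry results in enough detail. The downside is that more events will be labelled moderate or severe than under the present wording.
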